### Feasibility

What are the eligibility criteria for the BCPPA intervention?Is remote delivery of BCPPA acceptable to people with PPA and other dementias?Can the BCPPA be delivered remotely, as intended?Do planned outcome measures show sensitivity to change pre-/post-/3 months post BCPPA?What are the barriers and facilitators to implementation of BCPPA in an NHS setting?What is the optimal sample size for a future effectiveness study?What is the most appropriate analysis and method to measure costs and outcomes in a future trial?

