Conversation samples were selected as further secondary outcomes measures both to enable the measurement of change in conversation behaviours (both in the person with dementia and their CPs) and as the most proximal measure to the BCPPA intervention. Video recordings of natural conversations between the person with dementia and their CPs will be coded by raters masked to pre-intervention/post-intervention timepoints. They will identify and count conversation behaviours using an approach developed for use in BC intervention studies^50^ and previously used in the BCPPA study.^29^ Given the time-consuming nature of this outcome measure, a comparable clinical measure, the Kagan Measure of Skill in Conversation–Dementia and Measure of Participation in Conversation–Dementia Scale,^51^ will also be used for comparison. Video recordings will also be used for masked assessors to administer the Progressive Aphasia Communication Toolkit (PACT).^52^ PACT is designed for people living with conditions that result in progressive communication change, such as dementia and PPA. PACT documents and monitors symptom progression or treatment responsiveness using qualitative report and scales that evaluate strengths and needs across the communication domains: speech-voice, language, social-pragmatics and discourse.

Quality of caregiver–patient relationship^53^ measures change in both participants’ relationship to one another. Relationship was identified by the PPI advisory group as an important domain to consider.

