### Analysis plan

Qualitative and quantitative analysis will be used for this single masked, randomised controlled pilot study. Descriptive statistics will be used to report recruitment, attendance, attrition and reasons for dropout. A CONSORT^59^ and SPIRIT ^60^ flow chart will be used to present overall recruitment to and progression through the study (figure 1). Recorded intervention sessions will be transcribed, and descriptive statistics will be used to analyse dosage. Data collated from potential and actual participants, including date of onset, will also be examined to explore patterns related to optimal dosage and schedule of the intervention. Recruitment and retention rates will be used to support sample size calculations to inform a future full trial and plan the required number of sites to meet this target. Adverse events will also be recorded, and participant interviews examined to inform future recruitment procedures.

All outcome data will be explored to test for assumptions of normalcy. If assumptions are not met, appropriate non-parametric tests will be used. Repeated-measures analyses of variance will be used with group (immediate vs deferred) as a between-subject factor and time (pre-therapy and post-therapy) as a within-subject factor. Results will be used to determine a suitable and sensitive outcome measure and perform a power calculation to determine the sample size for a fully powered trial. Conversation data will be analysed following a procedure developed for the BCA intervention^29^ to identify change in the use of targeted strategies following intervention. This will involve counting barrier and facilitator behaviours in 5 min video samples selected from the pre-intervention and post-intervention conversation samples. These counts will be analysed using Poisson trend tests suitable for observations occurring in Poisson distribution. All pre-therapy conversations will be weighted the same as one another, as will all the post-therapy conversations. Outcomes for different participants will be investigated using a test for homogeneity, and where this is significant, the effect for different dyads will be calculated using the Holm–Bonferroni procedure.

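### Dyad-level conversation effects are to be obtained from Holm–Bonferroni, which yields no estimate, and only if a homogeneity test is significant; report each dyad's rate ratio with an interval regardless

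*Protocol article*

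**What the plan says.** In the protocol article, the Analysis plan describes the conversation analysis as a sequence. Its purpose is "to identify change in the use of targeted strategies following intervention". The data come from "counting barrier and facilitator behaviours in 5 min video samples selected from the pre-intervention and post-intervention conversation samples". The method is stated as "These counts will be analysed using Poisson trend tests suitable for observations occurring in Poisson distribution", with equal weights within each period: "All pre-therapy conversations will be weighted the same as one another, as will all the post-therapy conversations".

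Differences between dyads come next: "Outcomes for different participants will be investigated using a test for homogeneity". The dyad-level step is then conditional: "where this is significant, the effect for different dyads will be calculated using the Holm–Bonferroni procedure". The article names no dyad-level effect measure or interval. It also gives no alpha for the homogeneity test, no number of 5-minute samples per dyad and no expected counts.

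The Outcome measures section lists conversation samples as a secondary outcome and describes them "as the most proximal measure to the BCPPA intervention". The Sample size section plans 36 dyads. The Analysis plan refers to an earlier published procedure, which is cited but not reproduced.

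**The concern.** The sentence has two faults that can be seen without any data.

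- **The tool.** Holm–Bonferroni takes a set of p-values and returns adjusted p-values or rejection decisions. It cannot calculate an effect. Followed literally, the output is a list of dyads that pass a threshold, with no indication of how much each changed or how precisely that is known.
- **The gate.** A homogeneity test asks whether the change differs between dyads. A non-significant result is compatible with every dyad having changed by the same amount, with none having changed, or with real differences that the counts are too small to show. The plan treats these cases alike and produces no dyad-level result.

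A further consequence follows for counts. Whether a dyad passes a multiplicity-adjusted threshold depends on how many behaviours were coded as well as on the proportional change. Two dyads with the same true change can therefore be classified differently because one has more coded behaviours.

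At stake is the description of individual change on the outcome that the article regards as closest to the intervention. A pilot benefits more from sizes and spread of change than from a list of significant dyads.

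**Working it through.** The plan states no figure for this step, so there is none to reproduce. The checks below show how the stated rule behaves.

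**Inputs from the article.** 36 dyads (Sample size); pre and post counts with a Poisson test, a homogeneity gate, then Holm–Bonferroni (Analysis plan).

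**Assumptions.** Alpha 0.05 for the gate and for Holm; a family of 36 dyad tests (18 as an alternative); equal recorded time before and after; Poisson counts; an exact conditional binomial test per dyad; a chi-square test of the post-therapy share across dyads as the gate. Pre-therapy counts are varied because the article gives none.

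**1. Holm threshold.** The first step is 0.05/36 = 0.00139. If all n behaviours of a dyad fall in one period, the two-sided p-value is 2 × 0.5^n. For n = 10 this is 2/1024 = 0.00195, which is too large. For n = 11 it is 2/2048 = 0.00098, which passes. So at least 11 coded behaviours are needed, even in the most extreme split. With 18 dyads the threshold is 0.05/18 = 0.00278 and at least 10 are needed.

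**2. Power for one dyad whose count truly halves (rate ratio 0.5).**

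| Pre-therapy mean | Unadjusted 0.05 | First Holm step, 36 dyads |
|---|---|---|
| 5 | 7% | 0.1% |
| 10 | 18% | 1.3% |
| 20 | 37% | 5.6% |
| 40 | 70% | 23% |
| 80 | 95% | 66% |
| 160 | >99% | 98% |

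The true effect is the same in every row. Only the count differs.

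**3. How often the gate opens** (36 dyads, simulated):

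- Every dyad halves: 3–5% of runs. With a common rate ratio of 0.6: about 4%. Every dyad changed, yet dyad results are almost never produced.
- Half the dyads halve and half do not change (pre-therapy counts log-normal, log-SD 0.6): about 27%, 63%, 96% and 100% at median counts 5, 10, 20 and 40.

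**4. Who is flagged once the gate has opened.** Here dyads have pre-therapy means of 5, 10, 20 or 40 (nine each), and rate ratios vary around 0.6.

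| SD of log rate ratio | Gate opens | Flagged at mean 5 | Flagged at mean 40 |
|---|---|---|---|
| 0.3 | 68% | 0.2% | 18% |
| 0.5 | 99% | 0.3% | 25% |

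Both count groups draw from the same distribution of effects, so the contrast comes from the counts.

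**5. What an estimate would show instead.** For 20 behaviours before and 10 after, the rate ratio is 10/20 = 0.50. The standard error of its log is √(1/20 + 1/10) = 0.387. The 95% CI is 0.50 × exp(±1.96 × 0.387), that is 0.23 to 1.07. For 80 and 40 the ratio is again 0.50, the standard error is √(1/80 + 1/40) = 0.194, and the CI is 0.34 to 0.73. The reader sees the same estimated change with different precision, where the flagging rule would tend to separate the two dyads.

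**The case against.** The strongest defence is that the sentence is shorthand. Read in sequence, it means a Poisson test per dyad with Holm-adjusted p-values, and that does identify dyads with significant change when the gate opens. This stands. A reader might infer that the plan cannot show which dyads changed; the text does not support that, and step 2 shows good power if counts are high. Table 3 describes three 10-minute home recordings per assessment, so several 5-minute samples may be pooled for each dyad.

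A reader might also infer that the list of flagged dyads would be misleading. Under pure Poisson counts this is not shown. In the scenario where half the dyads respond, 98–99.7% of Holm-flagged dyads at medians 10 to 40 were true responders, although only about 3%, 11% and 32% of true responders were flagged. The reassurance rests on the Poisson assumption: with no true change and gamma overdispersion of 0.1 or 0.25, the gate opened in 98% or 100% of runs and 14% or 31% of dyads with mean 40 were flagged. Low power at low counts is a property of any count test, and a confidence interval does not remove it.

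Flagging rates computed with every dyad halving should not be cited as the plan's behaviour, because in that setting the gate would nearly always stay shut.

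It is also tempting to say that this step fails the feasibility question "What are the eligibility criteria for the BCPPA intervention". The article never assigns the step to that question. Reasons for exclusion, attendance, dropout and interviews are recorded under the acceptability assessment, and no criterion for success uses dyad-level conversation results.

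Finally, the cited procedure or a fuller plan may name an effect measure. That may be so, and the article does not say that rate ratios will be withheld. But the point is not a missing detail: the sentence names a tool that cannot do what is asked of it and states a condition that answers a different question.

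**Conclusion.** The point holds as a modest reporting correction to a secondary outcome. Two parts need no assumption: Holm–Bonferroni does not calculate effects, and a homogeneity test is the wrong condition for showing dyad-level change. As written, the plan provides no size or precision for any dyad's change. It provides nothing at dyad level when dyads change alike, where the gate opens at about its nominal 5% or less.

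The remaining sizes depend on assumed counts. With half the dyads halving, the gate opens in about 27% or 63% of trials at medians of 5 or 10, and in 96% or more at medians of 20 and above. The gate is therefore a serious obstacle to showing mixed response only if counts are low. The tilt towards dyads with many coded behaviours appears throughout the range examined, but its extent in this trial cannot be stated from the article.

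**What to change.** Replace the conditional sentence in the Analysis plan so that:

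- each dyad's post:pre rate ratio with a 95% confidence interval is reported whatever the homogeneity test shows, using an exact interval where counts are small;
- the homogeneity test, or a simple between-dyad variance, is kept as a description of variation and not as a gate;
- Holm–Bonferroni is used only to adjust any dyad-level p-values that are quoted, with the size of the family stated.

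A random-effects prediction interval and a display by diagnosis group are optional.

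The cost is a change of wording and a little extra analysis of data that will be coded anyway. The downside is that many individual intervals will be wide, as the 0.23 to 1.07 example shows, and the report should say so.

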### Criteria for success

This research will be considered appropriate to proceed to a full effectiveness study if:

The RA, local SLT collaborators and participants report positive views on remote delivery of BCPPA and other rare dementias.Participant recruitment and retention targets are achieved within the designated time frame.An appropriate outcome measure is determined and sample size estimated.An appropriate perspective of analysis and measurement of costs is determined for a future cost-effectiveness analysis.

## Ethics and dissemination

This study will be conducted in line with the Declaration of Helsinki and ethical approval was granted by the Health Research Authority for England and Wales IRAS Project ID: 341322 REC REF 24-NI-0123. A minor amendment to add the PACT outcome measure was approved on 17 October 2025 (ref EA-102907). This study is sponsored by the University College London Joint Research Office, UCL, [name]. Results from this study will be shared at conference, published in peer-reviewed journal articles and shared with participants and PPI advisors in accessible coproduced formats.

### Informed consent

All practicable support will be provided to assist potential participants, including appropriate care and facilitation to explain the research and support understanding, and sufficient time to allow prospective participants to reach a decision. Participants will be excluded if they lack capacity to consent at the outset of the study. The BCPPA and other rare dementias intervention is relatively brief (3–6 weeks), and the total period of involvement in the study is maximally 31 weeks. It is not anticipated that participants’ decision-making capacity will change significantly during this period. However, this will be reviewed at every contact over the 31-week duration of their involvement. As per current Medical Research Council and National Institue for Health and Care Research (NIHR) Complex and alternative consent pathway guidance, no participant will be excluded from the study just because they no longer have capacity, and where participants’ decision-making capacity changes, their CPs will be invited to give their opinion as a consultee at this time.

Informed consent will be obtained by the RA at the primary research site or by the local collaborator (SLT) delivering intervention at the participating sites where therapy is being delivered. The current guidance from the Mental Capacity Act 2005^62^ and Royal College of Speech and Language Therapists^63^ regarding gaining consent from people with communication difficulties will be followed. The chief investigator, RA and local SLT collaborators all have considerable experience of working with individuals with communication and cognitive impairment. They also complete annual mandatory training on the Mental Capacity Act 2005^62^ and issues related to obtaining consent. All team members, including junior researchers involved in the study, must participate in a training session about consent processes. This will include problem-based support on a case-by-case basis throughout the study. If any team members have any doubts regarding the capacity of a person with dementia to provide informed consent, advice will be sought from the chief investigator, RA, or as per standard practice, an appropriate clinician who is familiar with the participant (eg, GP).

Participant information sheets and consent forms have been designed to be dementia and aphasia friendly to support the process of gaining informed consent. These have been designed using a resource for researchers in communication disability ‘engaging people who have aphasia’^64^ and modified with advice from people with dementia and their carers in the PPI advisory group. Throughout the interactions with all participants, clinicians will speak slowly and clearly; repeat information where necessary and ask open as opposed to closed questions.^65^ Importantly, as per the opinions of the PPI advisory group, people with dementia and their CPs will consent to accessible forms to ensure equity in the consent process.

It will be made clear to participants that no disadvantage will accrue if they choose not to participate. Consent has to be regarded as a continuing process rather than a one-off decision, and willingness to continue to participate in the study will be continually checked through discussion with participants. Should any person with dementia or their CPs show verbal or non-verbal indications of refusal or reluctance to participate in sessions or assessments, the CI, RA or local collaborator will revisit their decision to be involved in the study. Should they continue to decline participation in the study, then they will be withdrawn.

In line with the Mental Capacity Act 2005,^62^ MCA Code of Practice 2007^65^ and advice from the project PPI advisory group, the process for obtaining consent for each potential participant, both people with dementia and their CPs, will be as follows:

The potential participants (participants with dementia, their CPs and healthcare professionals) will receive the ‘Participant Information Sheet’ about the study from the recruiting RA or local SLT collaborator by email or equivalent (eg, posted or handed to them) at least 48 h prior to a face-to-face discussion with them.The participants and RA or local SLT collaborator will meet face-to-face to discuss the Participant Information Sheet and explain the project in more detail, giving the opportunity for the person to ask questions.The RA or local SLT collaborator will judge the quality of the person’s decision to participate in the study by asking the person to tell them about the purpose of the study, reason they have arrived at their decision and reasons for and against participating in the study. If the person is able to reach a decision about agreeing or refusing to participate in the study, the clinician will accept the person’s decision. They will make it clear that the person has the right to refuse to participate or withdraw from the study at any point and that this will not disadvantage them in any way. Participants will be reminded about their right to withdraw by the chief investigator, RA or local collaborator during every contact point throughout the study.If the person decides to participate in the research and they are judged as having the capacity to make this decision, they will be asked to sign and return the participant consent form to the RA. Each participant will be given a copy of the information sheet and sign the consent form for keeping. The original copy of the consent form will then be kept in their paper file in a locked cabinet at UCL. A digital copy of the consent form will also be made and stored on an encrypted external hard drive for study purposes.

In line with the MCA 2005, and in the unlikely event that a participant’s level of impairment increases significantly during the period they are involved in the study, and changes in capacity to consent to participation were to occur, the following process will be followed:

If the RA, local SLT collaborator or junior researcher has any doubts regarding the capacity of a person with dementia to provide informed consent, capacity to consent will be revisited by the RA or local SLT collaborator. As per current MRC and NIHR Complex and alternative consent pathway guidance, no participant will be excluded from the study just because they no longer have capacity, and where participants’ decision-making capacity changes, their CPs will be invited to give their opinion as a consultee at this time. In line with the MCA 2005,^62^ the consultee by virtue of having been recruited as a CP is defined as ‘interested in P’s welfare’.CPs who are prepared to be consulted will be invited to consider what they think the views of the person with dementia would have been if they had capacity. They will be given a 'consultee’ information sheet and asked to complete the consultee declaration for the continued participation of their relative in the research.The CP (consultee) will be able to withdraw the person with dementia from the study at this time or any time after this.Any person with dementia showing verbal or non-verbal indications of refusal or reluctance to participate in the focus group will be withdrawn from the study.

Should any person with dementia or their CPs show verbal or non-verbal indications of refusal or reluctance to participate in sessions or assessments, the chief investigator, RA or local SLT collaborator will revisit the participant’s decision to be involved in the study. Should they continue to decline participation in the study, then they will be withdrawn. If the partner of a person with dementia withdraws from the feasibility trial, then the person with dementia will have to withdraw also, as the intervention is completed together.

The RA or local collaborator will explain that participants are under no obligation to enter the trial and that they can withdraw at any time during the trial, without having to give a reason and without prejudicing his/her further treatment. Data and samples collected up to the point of withdrawal can only be used after withdrawal if the participant has consented for this. If a participant is required to re-consent or new information is required to be provided to a participant, the chief investigator must ensure that this is done in a timely manner.

## Discussion

This phase II mixed-methods process evaluation study in the form of a randomised controlled feasibility study comparing the BCPPA CPT intervention to a deferred entry group for people with PPA and other dementias and their CPs will inform a future full effectiveness study. Although a recent systematic review of CPT for dementia identified five randomised controlled trials,^26^ none of these described CPT interventions were delivered to both the person with dementia and their CPs; rather, these interventions focused on training solely the care partner. Other than the BCPPA pilot study^29^ that preceded this study, to our knowledge, no previous randomised controlled trials have explored the effectiveness of CPT for people with dementia.

The previous BCPPA pilot study demonstrated that a sample size calculation for a future effectiveness study would need to recruit at least 64 participants to demonstrate a reduction in the impact of aphasia on the measurement tools used in that study (using the Aphasia Impact questionnaire^34^). Importantly, participants and SLTs delivering the intervention reported that this measure did not accurately represent the full benefits of the intervention. This study is therefore informed by recent core outcome sets for PPA that highlighted the importance of ‘having conversations with families and friends’ as a priority outcome.^18^ This study will trial a range of outcome measures that aim to capture these constructs. We anticipate that the inclusion of a double baseline and 3-month post-intervention follow-up will provide a more accurate representation to inform the selection of a primary outcome measure and a future sample size calculation. Unfortunately, only one of the measures being employed in this study has been designed for and with people with PPA and other rare dementias. To counter this, several measures have been selected, and amendments were made to include the most up-to-date measures where possible.

The results of this study will be disseminated via presentations at national and international conferences and submitted for publication in peer-reviewed scientific journals. With support from the study steering committee, results will be disseminated through professional and user group networks via publications and presentations, for example, at the PPA support group branch of the Rare Dementias Support Group based at UCL (http://www.raredementiasupport.org/) and via the annual international PPA awareness campaigns (https://speechtherapyppa.com/ppa-awareness-day).

Given the advent of disease-modifying interventions for AD that at present have the potential to support people to live between 6 and 18 months longer, there is an urgent need for interventions that can also support people to live well. We anticipate that future studies might need to explore the combined impact of disease-modifying pharmaceutical options alongside non-pharmacological psychosocial treatments such as CPT to provide optimal outcomes and genuinely reduce the risk of negative health outcomes.
